## Methods/Design

### Study Design

The study is designed as multicenter prospective randomised controlled trial in a three-factorial, split-plot plan (3x3xn) characterized as profile analysis (Figure 1) [38]. Thereby "aftercare treatment" appears as whole-plot factor with three categories respectively study arms (booklet, IRENA, RÜCKGEWINN) crossed with the sub-plot time factor that has also three categories (before and after rehabilitation and 12 month follow-up) [39]. The aftercare treatments will be carried out between 2^nd ^and 3^rd ^measurement. The third factor is the nested patient factor and is treated as random [40]. In addition, we stratify and control the trial for the covariables "chronicity staging", "gender", "rehabilitation facility" and "aftercare facility". Therefore, these covariables appear as additional factors.

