### Randomisation and Data management

In consideration of the logistic situation with several external and internal recruiting rehabilitation facilities and the provision of aftercare in diverse residential areas with miscellaneous aftercare patients in each aftercare facility, specific demands arise for the data management and the randomisation procedure. To accomplish a realisation with high scientific quality, we chose a largely electronic and internet-supported solution for data management including an online-randomisation feature. We implemented a data base for partly electronic data capturing where participants and patients not participating with the right inclusion diagnosis must be registered by the rehabilitation practitioners via a web-application. For an estimation of the participation ratio, all patients who meet one of the inclusion diagnoses are counted anonymously, independent of their participation in the study or any exclusion criterion. Registration of participants must be done before allocation is accomplished by the study software, so allocation concealment is assured automatically. For sequence generation we used an urn randomisation algorithm [66]. This algorithm is the most widely studied member of the family of adaptive biased-coin designs and provides a good compromise between controlling multivariate experimental bias and balancing the trial [67]. Advantages are good statistical properties, which force a small sized trial to be balanced and approaching complete randomisation as the sample size increases, with less vulnerability to allocation bias than permuted-block design. Consequently, an additional practical capability arises. The urn randomisation allows stratification for either large or small number of covariables with unknown prevalence. In this trial we stratify the randomization for "chronicity staging" with 3 subcategories, "gender" with two subcategories and "rehabilitation facility" with six participating centres.

Further purpose of the electronic data management system is that, as a planning tool and tool for data transfer and communication with corresponding facilities, it allows to support the organisation of the aftercare groups.

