#### a) educational booklet

All participants in this study arm will receive an educational booklet from their rehabilitation practitioner in their dismissal examination as well as the advice to return to normal activities as soon as possible. As educational booklet, the German version of the "back book" of Burton et al. was chosen [68]. This booklet provides information about the new approach to back pain, causes of back pain, dealing with an attack of back pain, risk factors for development of chronic back pain and the role of activity. All information that is provided is in accordance with up-to-date scientific knowledge and is based on a bio-psycho-social model of back pain like described in Waddell [16].

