#### b) IRENA

All participants in this study arm will be introduced into the normal IRENA program (in German: Intensivierte Rehabilitationsnachsorge), which is usual care in Germany [71]. Every patient will be assigned to a certified outpatient aftercare facility near their residential area. Aftercare practitioners and patients can compile an individual therapeutic package from certain appointed therapeutic services [71]. Predominantly resistance training, gymnastics, aquatic exercise, back school and recreation exercises are prescribed by the physicians for aftercare. Most therapies are carried out in open access groups of at least 6 patients without being specific for medical indication. In the IRENA program it is possible to pass the intended 24 exercise sessions with varying frequency per week. Usually, participants complete two or three exercise sessions per week with duration of 90 to 120 minutes per session. Every aftercare facility offers specific therapy combinations at different days a week. Figure 2 shows a weekly therapy plan offered by one of our cooperating facilities.

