**target area III: improvement of health related physical fitness**	

III.a	Improvement of muscle strength and endurance of back and trunk muscles to prevent states of deconditioning dependent on on inactivity
III.b	Improvement of motor coordination of back and trunk muscles to increase spine stabilization
III.c	Improvement of whole body physical fitness (endurance, flexibility) in sense of enhancement of general physical health resources
III.d	Introduction to several types of physical activity
III.e	Development of a personal network for maintaining physical activity e.g. in fitness facilities

• resource-related mediation of knowledge,

• behavioural modulation and

• physical exercise

We determined the duration of RÜCKGEWINN at 6 months, taking into account the time necessary for the process of behavioural change. In order to have an equal number of sessions compared to IRENA, one session is scheduled weekly for 26 weeks. RÜCKGEWINN will actually be provided in two phases, with the first carried out in 10 consecutive sessions in closed groups. We chose the closed group form, because it is more appropriate to appeal on relevant factors of behavioral change, especially in terms of coping strategies and physical activity enhancement. For anticipated organizational reasons, the second phase of 16 sessions is planned as open access group with partly repeating contents, with the goal set at the participants' empowerment to regular self-determined health enhancing physical activity.

We developed a RÜCKGEWINN manual for therapists and provided some media like for example little ring binders with information cards for participants that will be handed out consecutively each session. We trained several therapists from cooperating certified aftercare facilities to our curriculum. Every patient of this study arm will be allocated to one of those facilities as close as possible to their residence respectively subject to their choice.

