### Statistical Hypotheses and Analysis

The primary question refers to the efficacy of the aftercare interventions in comparison to each other. This is related to treatment differences concerning the primary outcome (FFbH-R) during aftercare interventions and quantified by an interaction effect of the corresponding categories of the factors study arm and time between second and third general assessment. Furthermore, the additional single change over time in rehabilitation phases compared to the change effect of aftercare treatment and overall treatment efficacy of rehabilitation plus aftercare intervention should be evaluated for each aftercare treatment. In consideration of adjusting respectively maintaining the multiple α-error for the mentioned aims, multiple hypotheses will be tested in a closed test procedure [72]. Consistent with these objectives and the chosen factorial split-plot design with repeated measures, we use a saturated linear mixed effects model for statistical analysis and stratify for baseline and mentioned covariates [40,73]. To approach the linear change characteristics in two different phases (rehabilitation phases/aftercare treatment) as well as the total change, we use a structured additive linear mixed model with fractional polynomial b-splines with degree l = 1 (linear) and three knots κ_1 _- κ_3_, noted as follows [73]:

I: general form

Y=Uν+Xβ+Zγ+ε

II: reformuled

$$\begin{array}{l} y_{ij}=\beta_{0}+\gamma_{0i}+\beta_{1}t_{ij}+\beta_{2}t_{ij}I_{i}+\beta_{3}t_{ij}R_{i}+\gamma_{1i}t_{ij}+\nu_{1}T+\nu_{2}TI_{i}\\ \;\;+\nu_{3}TR_{i}+\beta_{4}AF_{i}+\beta_{5}RF_{i}+\beta_{6}MPSS_{i}+\beta_{7}G_{i}+\varepsilon_{ij} \end{array}$$

I_i _denotes the indicator variable for IRENA aftercare treatment and R_i _the indicator variable for RÜCKGEWINN aftercare treatment of individual i in a dummy coding with "booklet control" as reference category [73]. The corresponding *β_2 _*and *β_3 _*reflect directly the difference in "slope" of IRENA respectively RÜCKGEWINN to reference "booklet control" and for that reason the efficacy. AF an RF are dummy coded expressions for aftercare respectively rehabilitation facility of patient i, MPSS is also dummy coded variable for chronification stage according to Gerbershagen and G is a dichotomy gender variable. T denotes a suitable construction term for the b-spline for the additional effect (slope) of rehabilitation phases [73].

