At first hierarchical, global level in a closed test procedure a likelihood ratio test of the shown specified model against a zero model m_0 _is used with the following global linear hypotheses:

$$H_{0}:C_{AB}\beta =0\;\;H_{1}:C_{AB}\beta \neq 0$$

C is a suitable contrast matrix of fixed interaction effects:

$$C_{AB}=\left(\begin{array}{cccccccc} 0 & 0 & 1 & 0 & 0 & 0 & 0 & 0\\ 0 & 0 & 0 & 1 & 0 & 0 & 0 & 0\\ 0 & 0 & 1 & -1 & 0 & 0 & 0 & 0 \end{array}\right)$$

At second level of the test procedure, three single primary comparisons of change in functional capacity (FFbH-R) during aftercare treatments are performed with *β_i _*~*t(μ,σ^2^)*.:

$$\begin{array}{l} H_{0}:\beta_{2}=0\\ H_{0}:\beta_{3}=0\\ H_{0}:\beta_{2}-\beta_{3}=0 \end{array}\;\;\;\begin{array}{r} H_{1}:\beta_{2}\neq 0\\ H_{1}:\beta_{3}\neq 0\\ H_{1}:\beta_{2}-\beta_{3}\neq 0 \end{array}$$

As shown in the specified model, we consider the stratified analysis to be the primary analysis carried out with the corresponding intention to treat collective. Other analyses are conducted as sensitivity analyses.

To address secondary objectives of the study, the change of secondary outcomes in different aftercare treatments is also assessed. In order to identify effective components or partial goals that should be targeted in aftercare exercise programs, the time varying influence of secondary outcomes on the primary outcomes in the different treatments is modelled by multiple regression modelling.

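### The primary model adjusts every patient for aftercare facility, which follows from the allocated arm and does not exist for the booklet arm

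*Protocol article*

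**What the plan says.** The Study Design section names four covariables: "we stratify and control the trial for the covariables 'chronicity staging', 'gender', 'rehabilitation facility' and 'aftercare facility". It adds that they enter as further factors. The section Randomisation and Data management names three: "In this trial we stratify the randomization for 'chronicity staging' with 3 subcategories, 'gender' with two subcategories and 'rehabilitation facility' with six participating centres". Aftercare facility is not among them.

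The section Statistical Hypotheses and Analysis prints the model with a term beta4·AF_i and no condition on arm, and defines it thus: "AF an RF are dummy coded expressions for aftercare respectively rehabilitation facility of patient i". The booklet arm is the reference for the treatment indicators I and R. On the status of this model the plan says: "we consider the stratified analysis to be the primary analysis carried out with the corresponding intention to treat collective".

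The Aftercare Treatments section describes where each arm is treated:
- Booklet: "All participants in this study arm will receive an educational booklet from their rehabilitation practitioner in their dismissal examination". No aftercare facility is mentioned.
- IRENA: "Every patient will be assigned to a certified outpatient aftercare facility near their residential area".
- RÜCKGEWINN: "Every patient of this study arm will be allocated to one of those facilities". The facilities meant are those whose therapists were trained in the program. Distance and patient preference decide among them.

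**The concern.** A covariate in the primary model of a randomised trial should be fixed before allocation and defined for every patient. Aftercare facility fails on both counts. The set of possible facilities depends on the arm, and one arm has none. An analyst who applies the printed equation must therefore decide what AF is for a third of the randomised patients, and the plan does not settle it. Depending on that decision, the term either brings an arm contrast into the level of the outcome or removes the reference arm from the fit. In neither case does it do what a facility adjustment is wanted for. It enters only as a main effect on level, so facility differences in change during aftercare, the period that the primary question concerns, remain unmodelled.

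**Working it through.** **1. The plan's own figure.** Inputs from Sample Size and Power Calculation: f = 0.27, alpha = 0.05, power 0.80, m = 8 fixed parameters. An F test with noncentrality f²·N and m − 1 = 7 numerator degrees of freedom needs N = 204 = 3 × 68, the stated figure. Then 68/0.60 = 113.3, rounded up to 114; 114/0.75 = 152; 3 × 152 = 456. The 7 degrees of freedom are inferred because they reproduce the figure. m = 8 equals beta0 to beta7, with AF counted as one parameter, and the contrast matrix C_AB has eight columns. The AF term is therefore built into the plan and is not a slip in one line.

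**2. Columns of the model.** Intercept, t, tI, tR, T, TI and TR make 7. Rehabilitation facility (six centres) adds 5, chronicity stage (three categories) 2 and gender 1, giving 15 without AF. The number of aftercare facilities is not stated; I assume 8. I also assume 68 patients per arm and measurements at months 0, 1 and 12.

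**3. Booklet coded as no facility (zero on all 8 dummies).** There are 23 columns and rank 23, so beta2, beta3 and their difference are estimable. The 8 dummies sum to I + R, because exactly the active-arm patients have a facility. The printed equation has no term in I or R alone, so this adds an intercept difference between the active arms and booklet.

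**4. Booklet treated as missing.** 152 of 456 recruited patients (33%), or 68 of 204 analysed, leave the fit. There are 7 facility dummies and 22 columns. Among the remaining patients I + R = 1, so t = tI + tR and T = TI + TR. Two columns are redundant and the rank is 20. Only beta2 − beta3 can be estimated.

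**5. Precision under the coding in step 3.** The answer depends on where the coding of t and T makes the arms share a mean.
- Shared at the first measurement (T = 0, 1, 1): across three illustrative covariance structures the standard errors of beta2 and beta3 rise by 0% to 6%.
- T = −1, 0, 0 with the same times: they rise by 7% to 16%. For example, under equal correlation 0.6 the standard error goes from 0.1207 to 0.1351, and to 0.1394 if the two active arms use separate facilities (0.1351/0.1207 = 1.12; 0.1394/0.1207 = 1.15).
- Shared at the end of rehabilitation: a closed form serves. With variance σ² at the second and third measurement, correlation ρ and n per arm, the difference in change has variance 2σ²(1 − ρ²)/n with a common mean and 4σ²(1 − ρ)/n without. With separate facilities the standard errors are in the ratio √(2/(1 + ρ)). With facilities shared by both active arms only the active-versus-booklet level is freed, and the ratio is √(1.5/(1 + ρ) + 0.25).

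| ρ (assumed) | separate facilities | shared facilities |
|---|---|---|
| 0.8 | 1.054 | 1.041 |
| 0.6 | 1.118 | 1.090 |
| 0.4 | 1.195 | 1.150 |
| 0.3 | 1.240 | 1.185 |

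The overall range is thus 0% to roughly 25%.

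**6. A pre-randomisation substitute.** With a variable defined for everyone, such as residential catchment area (8 categories assumed), there are 22 columns and rank 22. The standard errors stay within about 1% of those without AF.

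**7. Parameter count after removal.** On the plan's way of counting, m = 7 gives 6 numerator degrees of freedom and N = 194, about 65 per arm, against 204 and 68.

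**The case against.** Several points on the other side are sound.

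- Losing a third of the sample needs a reading that the plan contradicts. Booklet is the reference category and the analysis is by intention to treat, so deleting that arm cannot be meant. This stands: coding booklet as no facility fits the text better, and the 33% is not the size of the problem.
- A reader might infer that conditioning on a post-randomisation variable biases the treatment effect, or that facility is wholly confounded with the treatment slopes. The documents do not support either. AF is constant over time and enters as a main effect, while the primary contrasts are differences in change.
- A reader might also infer that the arm main effect was left out on purpose and that AF undoes this. No section says so. The model is called saturated and aftercare treatment is the whole-plot factor, so an arm intercept breaks no declared restriction.
- The Study Design list need not mean a fourth randomisation stratum. The authors also use the word stratify for adjustment in the analysis. Three factors at randomisation and four in the model is a possible reading, which leaves loose wording rather than a firm contradiction.
- No sentence states that the facility is assigned after randomisation. It is inferred, but strongly: the RÜCKGEWINN pool is limited to trained facilities, so it cannot be settled before the arm is known. Booking patients into a facility while they are still in rehabilitation (Discussion) does not change this.

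An article may leave coding details to a fuller document. Here, however, it prints the equation, defines the term and makes the model primary. What is printed cannot be applied to the booklet arm without a further decision.

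**Conclusion.** The point holds in a limited form. The primary model adjusts for a variable that is determined by the allocated arm and undefined for the reference arm. Under the reading most consistent with the plan, the three primary contrasts remain estimable and no bias in them is demonstrated. The cost is an unannounced active-versus-booklet intercept, a standard error for beta2 and beta3 that is unchanged or up to roughly a quarter larger, and a facility term that does not address differences in change. The size rests on assumed facility numbers, measurement times, covariances and codings of T, none of which the article gives. Loss of the booklet arm, and with it beta2 and beta3, would follow only if AF were handled as missing, which the plan does not say.

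**What to change.** - Remove AF from the fixed part of the all-arm primary model, or replace it with a variable known before randomisation for every patient, such as residential catchment area. Keep chronicity stage, gender and rehabilitation facility.
- Align the list in Study Design with the three factors in Randomisation and Data management.
- If AF is removed, delete its column from C_AB. The entry is zero in all three rows, so the hypotheses do not change. Set m to 7. The requirement becomes N = 194, so the planned 204 analysed and 456 recruited suffice. If a substitute variable takes its place, m and C_AB can stay as they are on the plan's way of counting.
- Examine facility or group clustering in a sensitivity analysis, as a partially nested random effect on aftercare-phase change in the two active arms.

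The cost is small edits to the model, the contrast matrix, the parameter count and one sentence of the design section. No data collection or sample size increase is needed.

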**Methods/Design:**

This study aims to examine the efficacy of a specially developed bio-psycho-social chronic back pain specific aftercare intervention (RÜCKGEWINN) in comparison to the current usual aftercare (IRENA) and a control group that is given an educational booklet addressing pain-conditioned functional ability and back pain episodes. Overall rehabilitation effects as well as predictors for compliance to the aftercare programs are analysed. Therefore, a multicenter prospective 3-armed randomised controlled trial is conducted. 456 participants will be consecutively enrolled in inpatient and outpatient rehabilitation and assigned to either one of the three study arms. Outcomes are measured before and after rehabilitation. Aftercare programs are assessed at ten month follow up after dismissal form rehabilitation.

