However, the verification of long-term sustainability of achieved effects is missing so far [13]. For a long-term improvement of pain and functional ability, high intervention intensity or high volume, respectively, seems to be necessary (> 100 therapy hours), although it is not known in which period of time this volume has to be provided [13,20,24]. For the same reason of non-satisfying long-term evidence, general effectiveness of inpatient rehabilitation for chronic back pain in Germany has been put into question [11,26]. In available national mainly uncontrolled studies, merly short-term rehabilitation effects with relatively low effect sizes are reported [11]. To date, only Dibbelt et al. were able to report more constant higher effect sizes for a multimodal rehabilitation program [15]. But these effects also were cut back in comparison to control group. As reasons for missing long-term effects of inpatient rehabilitation in Germany, different causes have been discussed by Hüppe et al., concerning masked effects, non-satisfying multimodal profile of treatment, missing individualization of treatment, insufficient treatment intensity and inadequate aftercare [11]. Taking into account the high intensity or volume that seems to be necessary for the improvement of relevant outcomes in chronic back pain, the last two mentioned reasons deserve particular attention. Apparently, inpatient and outpatient rehabilitation intensity or duration is not sufficient to accomplish enduring effects on desirable outcomes in chronic back pain. Nevertheless, considering necessary adaptations in the recommended relevant target areas and specific sub-goals for effective rehabilitation programs, this is not really surprising. Within the typical scope of mostly three to four weeks of rehabilitative intervention in Germany, long-lasting adaptations referring to physical capabilities as well as health-related behaviour patterns may be initiated, but are hardly achieved to the full extent [27-29]. However, in the sense of recreation of functional health, exactly these adaptations in physical capabilities and in health-related behaviour patterns are assumed to form the basis of positive health benefits [6,30]. Gerdes et al. go even further with their statement for rehabilitation aftercare in Germany [31]. They postulate that the real rehabilitation process just begins after the institutional phase is completed.

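### The primary model gives each patient only one straight line while the mean bends at the end of rehabilitation, so the reported standard errors of β2, β3 and β2−β3 may be miscalibrated

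*Protocol article*

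**What the plan says.** The protocol article plans three assessments per patient and treats the patient as a random factor: "The third factor is the nested patient factor and is treated as random" (Study Design). The primary model is written out in Statistical Hypotheses and Analysis. It is meant to separate two periods: "To approach the linear change characteristics in two different phases (rehabilitation phases/aftercare treatment) as well as the total change".

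The fixed part has a time slope and its arm interactions (β1, β2, β3) and a rehabilitation-phase term with its arm interactions (ν1, ν2, ν3): "T denotes a suitable construction term for the b-spline for the additional effect (slope) of rehabilitation phases". The patient-level part is γ0i + γ1i·t_ij. No term in T carries a patient index, and no covariance is given for ε_ij.

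The efficacy parameters are β2 and β3, which "reflect directly the difference in 'slope' of IRENA respectively RÜCKGEWINN to reference 'booklet control' and for that reason the efficacy". After a global likelihood ratio test, "three single primary comparisons of change in functional capacity (FFbH-R) during aftercare treatments are performed", namely on β2, β3 and β2−β3. The model as printed is declared primary.

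On timing, Background describes rehabilitation as "Within the typical scope of mostly three to four weeks of rehabilitative intervention in Germany", and the Abstract says "Aftercare programs are assessed at ten month follow up after dismissal form rehabilitation". Study Design labels the last assessment as a 12-month follow-up.

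**The concern.** The plan expects the average patient to change course at discharge but does not let individual patients do so. Some patients gain much from rehabilitation and some little. Where such a gain departs from one straight line through all three assessments, the random intercept and slope can absorb only part of it, and the rest goes into ε.

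The primary contrasts are differences in change from discharge to follow-up, so they use exactly the part of the covariance that is restricted. If the fitted covariance overstates the variance of that change, the t-tests are conservative and power is lost. If it understates it, false positives exceed 5%.

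**Working it through.** **Inputs from the article.** Three assessments; rehabilitation of three to four weeks (taken as 0.85 month); follow-up ten months after discharge. Real time is therefore 0, 0.85, 10.85. The analysed number is 68 per arm. The sample-size chain reproduces: 68/0.6 = 113.3, so 114; 114/0.75 = 152; 3 × 152 = 456. It rests on an F test with f = 0.27, not on this covariance, and is unaffected.

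**Assumptions.** The article gives no correlations between assessments and no coding of t. I assume equal variances, complete data, independent ε and T = min(t, end of rehabilitation). I leave out the facility, staging and gender covariates, and I consider each contrast on its own with a large-sample normal test.

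**Step 1, parameters.** The printed model has Var(γ0) = a, Cov(γ0,γ1) = b, Var(γ1) = c and residual variance s: 4 parameters. Three assessments have 3 variances and 3 covariances: 6.

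**Step 2, what is restricted.** With t1 = 0:
- Cov(Y2,Y3) − Cov(Y1,Y3) = t2(b + c·t3) = (t2/t3)·[Var(Y3) − s − Cov(Y1,Y3)]. In real time t2/t3 = 0.85/10.85 = 0.078. With unit variance and Cov(Y1,Y3) = 0.49 the gap is at most 0.078 × 0.51 = 0.040. Discharge and baseline must relate almost equally to follow-up.
- With occasions coded 0, 1, 2, Var(Y2−Y1) = c + 2s = Var(Y3−Y2). Change over a few weeks must vary as much as change over ten months.

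**Step 3, effect on the test.** For a true matrix S, the printed model settles at the V of its own form that minimises log|V| + tr(V⁻¹S). The arms share a baseline mean, so an arm contrast in D = Y3−Y2 is adjusted for Y1 with k = Cov_V(D,Y1)/Var_V(Y1). Then:
- reported variance = (2/n)·[Var_V(D) − Cov_V(D,Y1)²/Var_V(Y1)]
- actual variance = (2/n)·[Var_S(D) − 2k·Cov_S(D,Y1) + k²·Var_S(Y1)]
- error = 2·P(Z > 1.96 × SE ratio), where SE ratio = reported SE / actual SE; n cancels.

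Worked case, real time, correlations (T1T2, T1T3, T2T3) = (.7, .49, .7). The fitted V has variances 1.001, 0.982, 1.016 and covariances 0.707, 0.586, 0.597 in the same order.
- Reported: Var_V(D) = 0.982 + 1.016 − 1.194 = 0.804; Cov_V(D,Y1) = −0.121; 0.804 − 0.015 = 0.789.
- Actual: 0.600 − 2(0.121)(0.21) + 0.015 = 0.564.
- Unstructured: 0.600 − 0.21² = 0.556.
- SE ratio = √(0.789/0.564) = 1.18. Error = 2·P(Z > 2.32) = 2.0%.
- Actual SE against unstructured = √(0.564/0.556) = 1.007. For an effect with 80% power under the unstructured matrix (2.80 SE), power = Φ(2.80/1.007 − 2.32) = Φ(0.46) = 68%.

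**Step 4, range.**

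| Correlations | Real time: SE ratio, error | Occasions 0,1,2: SE ratio, error |
|---|---|---|
| .7, .49, .7 | 1.184, 2.0% (power 68%) | 1.017, 4.6% (power 79%) |
| .6, .5, .7 | 1.166, 2.2% (power 69%) | 1.084, 3.4% |
| .7, .5, .6 | 1.059, 3.8% (power 76%) | 0.946, 6.4% |
| .75, .6, .65 | 1.026, 4.4% | 0.932, 6.8% |
| .75, .6, .6 | 0.983, 5.4% | 0.907, 7.5% |
| .75, .5, .5 | 0.976, 5.6% | 0.877, 8.6% |
| .7, .6, .5 | 0.924, 7.0% | 0.895, 7.9% |
| .7, .65, .5 | 0.897, 7.9% | 0.875, 8.6% |
| .75, .6, .5 | 0.915, 7.3% | 0.870, 8.8% |
| .5, .5, .5 | 1.000, 5.0% | 1.000, 5.0% |

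In every row the actual SE is within about 1% of the unstructured one.

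**Step 5, second parameterisation.** Real time was used again, but with assumed variance components as shares of baseline variance: error 0.10-0.25, rehabilitation response 0.05-0.40, individual aftercare change 0-0.30. SE ratios run from 0.94 to 1.46 and error from 6.5% down to 0.4%. The extreme of 1.46 needs error 0.10, response 0.40 and no individual aftercare change. With error 0.25 (the article puts retest reliability above 0.75), response 0.10 and aftercare change 0.10, uncorrelated, the fitted residual is 0.296. So about half of the response variance (0.046 of 0.10) enters the residual. Timing of 0, 0.9, 12 months gives the same range. REML simulations (1,500 runs, 114 per arm) gave SE ratios of 1.12, 1.08 and 1.44 against 1.119, 1.071 and 1.463 predicted.

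**The case against.** A random intercept and slope is a standard longitudinal model, and the article nowhere says that ε_ij is independent. A fuller plan might specify robust standard errors, which would settle the calibration. That stands, and it makes the point conditional. A fuller plan could not, however, simply add an unstructured residual to the printed random effects: that needs 3 + 6 = 9 parameters for 6 moments.

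The size also rests on inputs that the article does not give. For (.7, .5, .6) the coding of t alone reverses the direction. Real time is the natural reading of a slope, and there several moderate sets lie between 4.4% and 5.6%. The real-time cases at 7-8% need baseline to predict follow-up better than discharge does. No single coding yields both the 12-point loss of power and the highest error. Simulation confirms the conservative direction clearly but the inflated one only weakly: 6.4% in 500 trials has a standard error of √(0.064 × 0.936/500) = 1.1 points. All of this stands.

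A reader might infer three stronger things that the article does not support:
- That the standard errors are wrong. They may be; under compound symmetry they are right.
- That the whole individual response is treated as error. The random intercept and slope absorb part of a lasting response.
- That the treatment estimate is biased. With complete data it is not. A bias of −0.07 to +0.04 SD appeared only when 40% of follow-up values were lost depending on the discharge score in opposite directions in two arms, a pattern that nothing in the article suggests.

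**Conclusion.** The point holds in conditional form. The random part is a printed choice in the primary model, not a detail left for later. Given independent residuals, it imposes on the covariance a restriction for which the article offers no reason and which bears directly on the discharge-to-follow-up contrasts.

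Under the assumed correlations the two-sided error lies between about 2% and 7-8% in real time and reaches about 9% in occasion coding. It is often near 5% in real time. The largest power loss found is about 12 points. Only the reported SE is affected: with complete data the estimate is unbiased and its true precision is almost unchanged. The article cannot tell which case applies, so a covariance that does not depend on the answer is preferable.

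**What to change.** In the primary model, replace γ0i + γ1i·t_ij with independent ε_ij by an unstructured 3×3 within-patient covariance over the three assessments. Keep the fixed part and the contrasts β2, β3 and β2−β3 as printed. Fit by REML, with Kenward-Roger or Satterthwaite degrees of freedom for the t-tests. Keep the random-slope model as a sensitivity analysis.

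Do not add a random coefficient on T instead: three random effects plus a residual need 7 parameters, and three assessments supply only 6 moments.

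The cost is one line in the analysis section, no new data, two more covariance parameters (6 instead of 4) for about 3 × 68 = 204 analysed patients, and a negligible loss of efficiency if the simpler structure is true.
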